### Concealment mechanism {16b}

Because randomization occurs using a digital tool, there is no human involvement, and the process is fully concealed from both study investigators and prospective participants until the study arm is assigned according to the 16a item.

### Implementation {16c}

Participants will be enrolled by the oncologists of the Medical Oncology Unit of the Urbino Hospital (PU, Italy). The allocation to the intervention program will be randomly assigned by statisticians, who will be blinded to participants’ information. Randomization will take place using a manual list accessed electronically via Interactive Web Response System (IWRS) after randomization eligibility is determined (Fig. 1).

## Assignment of interventions: blinding

### Who will be blinded {17a}

Patient allocation and intervention will not be blinded. The data collectors will be aware of the participants’ allocation during the physical fitness assessments (i.e., cardiorespiratory, muscular, and flexibility fitness), whereas the data collectors of the clinical, biological, and other outcomes are unaware of the participant’s allocation. However, data preparation, elaboration, and statistical analysis of primary and secondary outcomes will be performed by researchers and statisticians in a blinded manner.

### Procedure for unblinding if needed {17b}

The design is open-label with only outcome assessors being blinded so unblinding will not occur.

## Data collection and management

### Plans for assessment and collection of outcomes {18a}

The primary outcome is the improvement of the QoL assessed by the EORTC QLQ-C30 questionnaire [25]. Scores obtained by the questionnaire range from 0 to 100, with higher scores that indicate better quality of life.

The secondary outcome is the improvement of health-related parameters, including fatigue, anthropometric measurements, cardiac function indexes, and functional, psychological, and metabolic parameters. Fatigue will be assessed by the brief fatigue inventory (BFI) questionnaire; questionnaire scores range from 0 to 90, with higher scores associated with more severe fatigue. Anthropometric measurements in terms of body weight (kg), height (cm), BMI (kg/m^2^), and fat mass (%) will be assessed by bioelectrical impedance analysis using the same DC430MA DC 430 (Tanita Europe) model. Cardiac function will be assessed by echocardiography and speckle tracking imaging analysis. Measurements will include volumetric measure by the modified Simpson’s rule, Doppler measurement of mitral inflow (E and A waves), tissue Doppler lateral mitral annulus peak velocity (e′ wave), and speckle tracking peak global longitudinal strain. Heart rate variability (HRV) will be assessed by 24-h monitoring of mean heart rate (HR in bpm), total number of premature ventricular and supraventricular beats (as percentage of total beats), time domain HRV parameters (standard deviation of the averaged normal to normal intervals), root mean square of successive differences of normal to normal intervals, percentage of adjacent normal to normal intervals that varied by more than 50 ms (pNN50 in %), frequency domain, and total power HRV parameters.

Functional parameters will include muscle flexibility (assessed by sit and reach test) and strength (assessed by isometric hand grip strength test), proprioceptive recalibration (stabilometry analysis by mean square deviation of velocity from mean), posture balance (stabilometry analysis by Romberg quotient test—European variant) [26], upper limb muscle viscoelastic characteristic evaluation by a hand-held myotonometer, and cardiorespiratory fitness. Participants’ cardiorespiratory fitness will be assessed by estimating the maximal oxygen uptake (*V̇*O_2max_) using an individualized submaximal incremental walking test performed on a treadmill [20, 27]. The test will comprehend multiple 3-min stages with incremental exercise intensities individualized according to the predicted *V̇*O_2max_ of each individual. The walking speed, which will be individually chosen for each participant, will be kept constant throughout the test. Hence, treadmill grade will be modified at each stage to induce an exercise intensity of the first stage at about 30% of the predicted oxygen uptake (*V̇*O_2_) reserve (*V̇*O_2_R), with about 10% *V̇*O_2_R increase in exercise intensity for each stage. Exercise intensity will be increased until participants will reach 70% of HRR [27]. The HR or *V̇*O_2_ values corresponding to the desired percentages of the reserve values (%*V̇*O_2_R or %HRR) will be calculated as follows: (maximal value - resting value) x desired percentage + resting value. Resting *V̇*O_2_ will be assumed to be 3.5 mL∙min^-1^∙kg^-1^ [20], *V̇*O_2max_ will be predicted by means of a non-exercise model [28], and *V̇*O_2_ will be converted to treadmill speed and grade using the ACSM’s walking equation [20]. Resting HR will be measured after sitting for 10 min, while maximal HR (HR_max_) will be predicted as proposed by Gellish et al. [29]. Participants’ HR will be recorded at each stage and used to create individual submaximal HR-*V̇*O_2_ relationship which will be extrapolated to the predicted HR_max_ in order to estimate*V̇*O_2max_ [20, 27]. The individualized testing protocols will be created once at *T*_1_ and repeated at the following timepoints.

Psychological well-being will be assessed through the evaluation of mood profile change (Profile of Mood States (POMS) questionnaire). The analysis of metabolic, hormonal, and inflammatory risk factors will include Homeostatic Model Assessment for Insulin Resistance (HOMA-IR) Index, insulin-like growth factor (IGF-1), and C-reactive protein.

Gut microbiota will be assessed by the analysis of microbial diversity (NGS of the V3–V4 region of the 16S rDNA gene). Osteoporosis level will be assessed by computerized bone mineralometry (*T*-score). Recurrences free interval defined as time from registration to time of documented recurrent disease will be assessed.

Diet habits, physical activity level, pharmacological treatments, and comorbidity will be recorded as confounding factors and covariates. Change in dietary intake will be assessed by a questionnaire (14-item Mediterranean diet adherence screener, MEDIET) through the DIANAWeb platform [22, 30]. Change in physical activity level will be assessed by the SenseWear armband activity monitor (BodyMedia Inc., Pittsburgh, PA) that participants will wear for at least 5 consecutive days (24 h a day) and by the International Physical Activity Questionnaire Short Form (IPAQ-SF) [16, 17]. The output of both assessments will be expressed in metabolic equivalents (MET∙min∙week^−1^).

### Plans to promote participant retention and complete follow-up {18b}

Informative and social events will be organized to promote participant retention to complete the follow-up. Social events such as healthy dinners, cooking sessions, or walks are very important to create a group on a healthy lifestyle. Throughout the follow-up period, patients will take part in group chats and webinars on healthy nutrition and exercise behavior. From the moment of enrollment, all patients will be registered on the DianaWeb platform [22, 30], in which they will be invited to cook and eat some dishes prepared according to the WCRF/AICR recommendations and inspired by a Mediterranean diet. In addition, to promote participant retention, and to complete the follow-up, experts in oncology nutrition and exercise experts will stimulate the patients during the lifestyle intervention period (3-month) weekly through a social chat to adhere to the change in lifestyle with a short message service at the beginning of each session week and indicatively at each of the other time evaluation points (6-12-24-month). Feedback from patients about their experience with assessment and intervention procedures is often obtained in formative interviews, focus groups, or responses to questionnaires. Workshops, seminars, conferences, and cultural meetings on a scientific basis will also be organized throughout the planned trial period for “Training for well-being” dedicated to correcting lifestyles with particular attention to the psychological aspects, nutrition, and physical activity for the health and psycho-physical well-being of the cancer patient. One seminar a month to discuss a particular lifestyle issue, one workshop or conference on the preliminary results obtained involving the trial and external expert panel, and two-time events regular (usually annual) structured 5–10-km walks and social dinners. In addition, “experiential training courses in cooking” are planned to support therapies for the achievement and maintenance of the levels of psycho-physical well-being expected in the project. These training events also have a high power to also affect the aspects of prevention in the healthy population that may eventually be involved. The courses will be entrusted to highly qualified experts. This project will involve experts in physical exercise and cancer prevention with experience in multidisciplinary and professional management models that revolve around the cancer patient. In fact, in this area, the foundations of correct communication with the oncological patient are fundamental, which represents a factor that can positively influence the participant’s response to therapy.

### Data management {19}

Electronic case report forms (eCRFs) will be used to capture and organize data as defined in the study protocol. The system will include the eCRF to collect primary data and serve as a conduit to transfer sensitive data. A data management plan will be created before data collection begins and will describe all functions, processes, and specifications for data collection, cleaning, and validation. The eCRFs will include programmable edits to obtain immediate feedback if data are missing, out of range, illogical, or potentially erroneous. Concurrent manual data review will be performed based on parameters dictated by the plan.

### Confidentiality {27}

Individual participants’ medical information obtained as a result of this study is considered confidential and disclosure to unauthorized parties is prohibited. Participants’ confidentiality will be assured by utilizing unique participant numbers instead of names. If the results of this study will be reported in medical journals or at meetings or may be submitted to competent regulatory authorities in connection with regulatory procedures, the participants’ identity will not be disclosed. With the participants’ authorization, medical information may be provided to the participant’s personal physician or to other appropriate medical personnel responsible for the participant’s welfare.

In compliance with GCP guidelines, all participants will be informed of the purpose of the research, the possible risks, and their right to withdraw at any time from the study without prejudice and without jeopardy to their future medical care at the center. Each participant must agree to cooperate in all aspects of the study and must give informed written acknowledgment (signed ICF) to the investigator prior to participation in the study. If the ICF is revised during the study, active participants must sign the new version in order to continue participating in the study.

The investigator will maintain adequate records for the study including completed eCRFs, medical records, laboratory reports, signed ICFs, drug disposition records, adverse experience reports, information regarding participants who discontinued, all correspondence with the Institutional Review Board (IRB) and Independent Ethics Committee (IEC), and other pertinent data.

### Plans for collection, laboratory evaluation, and storage of biological specimens for genetic or molecular analysis in this trial/future use {33}

Serum samples will be anonymously stored for further molecular or biological activity analyses. Samples will be aliquoted to avoid freeze/thaw cycles and frozen at −80°C until their use.

## Statistical methods

### Statistical methods for primary and secondary outcomes {20a}

A mixed-design ANOVA will be used to compare the changes over time (from T1 to T2, within factor) in the primary outcome between intervention and control arms (between factor). The sample size was calculated to test the hypothesis of no differences between the changes in the primary outcome of the two groups (i.e., interaction effect of the between and within factors of the mixed-design ANOVA). If a significant effect is found, post hoc pairwise comparisons will be used.

Secondary outcomes will be analyzed using repeated measures MANOVA models, with difference-based contrasts.

For all tests, a 2-sided *α* level of significance of 0.05 will be used and, if necessary, the *α* level inflation due to multiple tests will be accounted for by using the appropriate correction (e.g., Bonferroni, false discovery rate, etc.). The statistical test assumptions will be assessed and, if not met, either data transformation or alternative statistical methods (e.g., GEE, non-parametric analyses, etc.) will be performed.

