### Outcomes {12}

Primary outcome measure:Quality of life assessed by questionnaire: change in the quality of life assessed by the European Organisation for Research and Treatment of Cancer Quality of Life Questionnaire (EORTC QLQ-C30). Scores ranging from 0 to 100; higher scores indicate better quality of life.

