### Sample size {14}

The sample size was calculated with the aim of verifying the differences between the QoL changes in the two groups (i.e., intervention and control arm), after 3 months of intervention.

The QoL expected improvement in the experimental group at 12 weeks is 15.1 ± 17.7, while in the control arm, it is 6.1 ± 17.1 [24]. Using a *t*-test for independent samples, with an alpha of 0.05 and statistical power of 0.80, to find differences in QoL improvements between the two groups at the end of the intervention, 60 participants per group will be needed. Considering an expected drop-out of 30%, a total of 172 patients will be recruited. The sample size was calculated using Stata statistical software (StataCorp. 2013. Stata Statistical Software: Release 13. College Station, TX: StataCorp LP).

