## Assignment of interventions: allocation

### Sequence generation {16a}

In order to ensure balanced groups, participants will be randomized to the two arms (with a 1:1 ratio) using permuted block (*n* = 4) randomization, stratified according to the anthracycline treatment.

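### The primary QoL analysis compares raw change and adjusts for neither baseline QoL nor the anthracycline stratum: valid and adequately powered, but it gives up precision that data already collected could supply

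*Protocol article*

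**What the plan says.** Four places in the protocol article bear on this point.

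- **Primary model, section {20a}.** "A mixed-design ANOVA will be used to compare the changes over time (from T1 to T2, within factor) in the primary outcome", with arm as the between factor. The hypothesis is tied to the "interaction effect of the between and within factors of the mixed-design ANOVA". No covariate or stratum term is named.
- **Randomisation, section {16a}.** Allocation is 1:1 in permuted blocks of four, "stratified according to the anthracycline treatment".
- **Sample size, section {14}.** The trial is sized by an independent-samples t-test on the QoL improvements. "The QoL expected improvement in the experimental group at 12 weeks is 15.1 ± 17.7"; the control-arm figure is 6.1 with SD 17.1. The result is 60 per group, or 172 in total with 30% drop-out.
- **Covariates elsewhere.** The data collection section {18a} lists diet, physical activity, drug treatments and comorbidity as confounders and covariates to be recorded. Section {20b} plans exploratory covariate analyses of the primary and secondary outcomes. Neither names T1 QoL or the anthracycline stratum, and neither puts a covariate into the primary model.

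**The concern.** Baseline QoL has to be collected, because the primary outcome is defined as a change. In a two-by-two mixed-design ANOVA it enters only by subtraction, which fixes the slope of T2 on T1 at 1. ANCOVA estimates that slope from the data. Where the true slope is below 1, subtraction over-corrects for baseline, and part of the baseline noise stays in the treatment estimate. The anthracycline stratum was judged important enough to balance at randomisation, yet it is absent from the analysis, so the model does not mirror the design.

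What is at stake is the width of the confidence interval and the power obtained from a fixed number of patients, in a trial that expects to lose 30% of them. The validity of the test is not at stake.

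**Working it through.** **Inputs from section {14}.** Changes of 15.1 (SD 17.7) and 6.1 (SD 17.1); alpha 0.05, two-sided according to {20a}; power 0.80; 60 per group; 30% drop-out.

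**Inputs assumed.** The article gives neither the T1-T2 correlation r nor the SD of QoL at either time. I take r from 0.3 to 0.8 with equal SDs at T1 and T2, and then relax the equal-SD assumption.

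**Step 1. Reproduce the plan's figure.**
- Difference: 15.1 − 6.1 = 9.0 points.
- Pooled SD of change: √[(17.7² + 17.1²)/2] = √302.85 = 17.40.
- Number per arm: 59 by the normal approximation, 60 by the exact noncentral t-test.
- Power at 60 per arm: 0.802.
- Total: 120/0.70 = 171.4, rounded up to 172. The plan's numbers are correct for its test.
- Standard error: 17.40 × √(2/60) = 3.18. The 95% CI half-width is 1.98 × 3.18 = 6.3 points.

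**Step 2. Variance with baseline adjustment.** With a common SD s at both times:
- Var(change) = 2s²(1 − r)
- ANCOVA residual variance = s²(1 − r²)
- Ratio = (1 + r)/2

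The adjusted SD is therefore 17.40 × √[(1 + r)/2].

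**Step 3. Results at 60 analysed per arm and a 9.0-point difference** (noncentral t, 117 df for ANCOVA):

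| r | Variance ratio | Adjusted SD | Power | CI half-width (points) | n per arm for 80% power | Implied T1 SD |
|---|---|---|---|---|---|---|
| raw change | 1 | 17.40 | 0.802 | 6.3 | 60 | – |
| 0.3 | 0.65 | 14.03 | 0.936 | 5.1 | 40 | 14.7 |
| 0.5 | 0.75 | 15.07 | 0.900 | 5.4 | 46 | 17.4 |
| 0.7 | 0.85 | 16.04 | 0.862 | 5.8 | 51 | 22.5 |
| 0.8 | 0.90 | 16.51 | 0.842 | 6.0 | 54 | 27.5 |

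The last column is 17.40/√[2(1 − r)], the T1 SD that each r implies if the change SD in the article is right. A simulation of 4,000 trials at r = 0.5 gave power of 0.81 for raw change and 0.91 for ANCOVA. Its variance ratio was 0.74, against 0.75 in theory.

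**Step 4. Relax equal SDs.** With SDs s₁ at T1 and s₂ at T2:
- Var(change) = s₁² + s₂² − 2r s₁s₂
- ANCOVA variance = s₂²(1 − r²)
- Difference = (s₁ − r s₂)²

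The difference is a square, so in large samples ANCOVA is never less precise. The gain vanishes when r s₂ = s₁. For example, with s₁ = 1, s₂ = 1.2 and r = 0.8, the variances are 2.44 − 1.92 = 0.520 and 1.44 × 0.36 = 0.518, which is practically no gain.

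**Step 5. Stratum term.** No calculation is possible. The article gives neither the proportion treated with anthracyclines nor any relation between that treatment and QoL.

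**The case against.** The strongest reply is that nothing here is wrong. Section {20a} tests the same contrast that section {14} sizes, the comparison is unbiased under 1:1 randomisation, and 60 per arm delivers the stated power. That stands, and it limits the point to efficiency. A reader might infer that chance baseline imbalance biases the result. It does not: the imbalance averages out over randomisations, and the change-score standard error already reflects it.

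The second reply is that the size of the gain is assumed. That also stands. The 0.94 at r = 0.3 requires a T1 SD of about 14.7, which nothing in the article supports or refutes, and under unequal SDs the gain can be close to nil. The direction is secure; the amount is not.

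The third reply is that covariates appear in {18a} and {20b}, and that a fuller protocol or an SAP might add terms. This holds only in part. The covariate analyses in {20b} are exploratory and name neither variable, while {20a} states a specific primary model.

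Some stronger readings are not supported:
- **That the stratum term is sure to add precision, or that leaving it out inflates the standard error.** A constant difference in QoL level between strata cancels in a change score. The stratum must predict QoL change, or T2 QoL after baseline adjustment, and the article is silent on this. Any inflation would be in the conservative direction.
- **That the post hoc comparisons will be before/after tests within each arm.** Section {20a} says only "If a significant effect is found, post hoc pairwise comparisons will be used" and does not define them.
- **That the fallback for failed assumptions must leave the points scale.** GEE is among the options listed and can stay on it.

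**Conclusion.** The point holds as an efficiency improvement at almost no cost. The planned test is valid and reaches 0.802 power. Baseline-adjusted ANCOVA on the same patients would raise power to between about 0.84 and 0.94, and shorten the CI half-width from 6.3 to between about 6.0 and 5.1 points. Those ranges rest on two assumptions that the article does not settle: r between 0.3 and 0.8, and equal SDs at T1 and T2. If the T2 SD is larger and r is high, the gain may be negligible, but in large samples there is no loss.

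The case for the stratum term is that the analysis should match the randomisation. It carries no promised gain in precision. A reader should not conclude that the trial is underpowered or that its primary result would be biased for this reason.

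**What to change.** In section {20a}, make the primary analysis an ANCOVA of T2 QoL on arm, T1 QoL and anthracycline stratum, or put the same terms into the repeated-measures model. Report the adjusted between-arm difference in points with its 95% CI.

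The cost is one paragraph and the ethics submission that section {25} requires for amendments. The change should be fixed before outcome data are examined by arm. No new data are needed, because T1 QoL and the stratum are already recorded. The target of 172 can stand, with any gain taken as extra power and a narrower interval.

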Secondary outcome measure:2.Fatigue: change in fatigue perception assessed by the brief fatigue inventory (BFI) questionnaire. The score of the questionnaire ranges from 0 to 90. A higher score means more severe fatigue.3.Anthropometry: change body mass index (BMI) expressed as kg/m^2^.4.Body composition: change fat mass (%) assessed by bioelectrical impedance analysis.5.Cardiac function indexes: change in the global longitudinal strain (%) assessed by echocardiography.6.Heart rate variability: change in heart rate variability assessed by 24-Holter monitoring.7.Cardiorespiratory fitness: change in cardiorespiratory fitness assessed by estimated maximal oxygen uptake (mL/min/kg).8.Flexibility: change in muscle flexibility assessed by sit and reach test (m).9.Muscular fitness: change strength assessed by isometric hand grip strength test (kg).10.Proprioceptive recalibration: change assessed by stabilometry (mean velocity) (mm^2^/s^2^).11.Posture balance: change assessed by stabilometry (Romberg Quotient test-European variant) (% over or under 100).12.Upper limb muscle viscoelastic characteristics: change in the muscle properties of the pectoralis major, upper trapezius, and sternoclavicular mastoid muscle assessed by a hand-held myotonometer.13.Psychological well-being: change in mood profile assessed by the Profile of Mood States (POMS) questionnaire. The POMS questionnaire gives a 5-point Likert scale; a higher score indicates increased negative mood.14.Homeostatic Model Assessment for Insulin Resistance (HOMA-IR) Index: change in HOMA-IR Index calculated as HOMA-IR = (FPI × FPG)/22.5, where FPI is fasting plasma insulin concentration (mU/L) and FPG is fasting plasma glucose (mmol/L), or as HOMA-IR = (FPI × FPG)/405 if fasting plasma glucose is expressed in mg/dL.15.Insulin-like growth factor (IGF-1): change in IGF-1 assessed by blood samples (μg/L).16.C-reactive protein: change in high sensitivity C-reactive protein assessed by blood samples (mg/L).17.Gut microbiota: change in microbial diversity (species diversity %) assessed by next-generation sequencing (NGS) of the V3–V4 region of the 16S rDNA gene.18.Osteoporosis level: change in computerized bone mineralometry assessed by *T*-score (normal: +2.5> *T*-score > −1.0; osteopenia: −1.0> *T*-score >−2.5; osteoporosis: *T*-score <−2.5; severe osteoporosis: *T*-score <−2.5 with one or more fragility fractures).19.Recurrences: recurrence-free interval defined as the time from registration to the time of documented recurrent disease.

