### Methods in analysis to handle protocol non-adherence and any statistical methods to handle missing data {20c}

This study will employ a per-protocol analysis in which missing data will not be imputed. Sensitivity analyses will be performed to assess the robustness of the results based on quantitative and qualitative levels of adherence to the exercise protocol. The main statistical analyses will be performed without considering the exercise protocol adherence. In accordance with the available literature (see Hawley-Hague et al. [31] for a methodological review on this topic), the three sensitivity analyses will be performed by including, in the statistical analysis, only the participants who completed at least 65, 70, and 75% of the total training sessions exercising at both the prescribed intensities (i.e., with an average exercise intensity of each session within 4 bpm of the prescribed HR [21]) and durations (i.e., with an exercise session duration within 5 min of the prescribed duration). The qualitative reasons for withdrawal from the trial or non-adherence to the exercise protocol will be recorded. Finally, to assess if the missing data and non-adherence to the exercise protocol are at random, exploratory analyses will be performed to assess the presence of patterns among the missing data, exercise protocol non-adherence, participants’ characteristics, and group allocation.

Trial retention will be scored as the rate of drop-out in the intervention group after signing informed consent for the study.

Cohort retention drop-out in the intervention and control group will be defined as withdrawal from the cohort and/or non-response to the regular cohort measurements and will be scored for both groups.

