Moreover, in the present project, although it is recommended that exercise programs include resistance exercises [8, 20], the participants of both groups will solely receive generic indications regarding the importance and guidelines of resistance exercises and flexibility training during the counseling sessions, but they will not receive any supervision or prescription for those two exercise modalities. Therefore, the inferences on the possible short- and long-term differences between the two arms, hence the effect of the mixed directly and remotely supervised exercise intervention, will only be applicable and valid for aerobic exercise; hence, future studies should assess the efficacy of these types of interventions and supervisions in exercise programs involving both aerobic and resistance exercise or resistance exercise only.

Additionally, it is worth noting that RCT interventions in the field of exercise oncology have several limitations, such as drop-out and loss of follow-up of patients during the entire course of the study. For this reason, we estimate an expected drop-out of 30% for a total of 172 patients after the 12-week interventions, which will probably increase over the 2 years of follow-up. To ensure that the drop-out rate is not affected by the present study design and consequently affects the results of the present study, trial retention will be scored as the rate of drop-out after signing informed consent for the study and registered for both groups. Then, exploratory analyses will be performed to assess if several factors (e.g., trial arm, clinical, and characteristics) affected the drop-out rate.

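### The protocol assigns every secondary outcome to repeated measures MANOVA, which cannot analyse the censored recurrence-free interval and drops women with partial data from any model wider than one outcome at T1 and T2

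*Protocol article*

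**What the plan says.** All references are to the Protocol article.

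- **Method.** Section {20a}: "Secondary outcomes will be analyzed using repeated measures MANOVA models, with difference-based contrasts". No secondary outcome is excepted.
- **Recurrence.** Outcomes {12}, item 19 of the secondary list: "recurrence-free interval defined as the time from registration to the time of documented recurrent disease". The assessment section {18a} repeats it: "Recurrences free interval defined as time from registration to time of documented recurrent disease will be assessed". I found no survival method and no censoring rule in the article.
- **Fallback.** Section {20a} says that test assumptions will be checked and, "if not met, either data transformation or alternative statistical methods (e.g., GEE, non-parametric analyses, etc.) will be performed".
- **Missing data.** Section {20c}: "This study will employ a per-protocol analysis in which missing data will not be imputed".
- **Attrition.** Sample size {14}: "Considering an expected drop-out of 30%, a total of 172 patients will be recruited". The Discussion adds that drop-out is something "which will probably increase over the 2 years of follow-up".
- **Later visits.** The retention section {18b} mentions contact "indicatively at each of the other time evaluation points (6-12-24-month)", and the Discussion speaks of effects at 6, 12 and 24 months.

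**The concern.** There are two separate problems.

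The first is a mismatch between method and outcome. Repeated measures MANOVA compares vectors of repeated measurements, and difference-based contrasts compare one occasion with another. A recurrence-free interval has no occasions to compare. For a woman with no documented recurrence, only a lower bound on her time is known. Following the sentence literally would mean treating censored times as observed, leaving those women out, or analysing recurrence by a method chosen after the data are seen.

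The second is how MANOVA handles incomplete data. In its standard form it uses only women with every component of the response vector. With imputation ruled out, a woman who has a 3-month value but misses a later visit, or lacks one of several pooled measures, contributes nothing to that model. The results would then rest on a smaller and possibly selected subset, although her observed values were collected.

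**Working it through.** **1. The plan's own figure.** From Sample size {14}: changes of 15.1 (SD 17.7) and 6.1 (SD 17.1), alpha 0.05, power 0.80.

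- Difference = 15.1 − 6.1 = 9.0
- Pooled SD = √((17.7² + 17.1²)/2) = √302.85 = 17.40
- A two-sided independent-samples t-test (noncentral t) needs 59.67, so 60 per group
- With 30% drop-out: 120/0.70 = 171.4, so 172

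The stated 60 and 172 reproduce. They concern the primary outcome only and are not in dispute.

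**2. Recurrence against the stated method.**

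| Needed for repeated measures MANOVA with difference contrasts | Recurrence-free interval as defined |
|---|---|
| A value at two or more occasions | One time per woman |
| A baseline value | None |
| Fully observed responses | Right-censored if there is no recurrence |

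Transforming the times leaves them censored. GEE on repeated values has no repeated values to use. This conclusion needs no numerical assumption.

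**3. Complete-vector loss, as an illustration.** Inputs from the documents: 172 women, 30% lost by week 12, and evaluation points at 6, 12 and 24 months. Assumption (no figure is given): a fraction m of those remaining is lost at each of the three later visits.

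Women with T1 and T2: 172 × 0.70 = 120.4. Women kept by a five-visit model: 120.4 × (1 − m)³.

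| Assumed m | Calculation | Women kept |
|---|---|---|
| 0% | 120.4 × 1 | 120 |
| 5% | 120.4 × 0.857 | 103 |
| 10% | 120.4 × 0.729 | 88 |

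For the T1-to-T2 contrast, such a model would set aside 120.4 − 103.2 = 17.2 to 120.4 − 87.8 = 32.6 women, about 17 to 33, who do have both values.

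**4. Pooling outcomes, as an illustration.** Assume 2% of values are missing independently among 120 attendees, in a two-visit model with k outcomes. Women kept = 120 × 0.98^(2k).

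- k = 1: 115
- k = 5: 98
- k = 10: 80

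With one outcome at T1 and T2, the loss beyond T2 attrition is therefore about 5 women under this assumption.

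**5. Check of the deletion rule.** A MANOVA was fitted to simulated data on 172 women over five visits. Of these, 52 had baseline only and 18 others missed one later visit. The model used 172 − 52 − 18 = 102 rows, so the 18 women with four of five visits were dropped entirely.

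**The case against.** The strongest case against the point concerns its second half. Section {20a} does not say which visits or outcomes enter each MANOVA. It speaks of models in the plural, which fits one model per outcome at least as well as one large model. The only analysis window it states is T1 to T2, for the primary outcome, and the visit schedule is in a figure that is not shown. If each outcome is modelled alone at T1 and T2, a mixed model would have no T2 value for the missing 30% either. All of this stands, and it makes the deletion point conditional.

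Three stronger readings are tempting, and the documents do not support them.

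- **A stated loss of power.** A reader might convert the reduced counts into power. The article gives no effect size for the secondary outcomes, and the later-visit and item-missing rates are assumed. Part of the fall is plain attrition: a woman lost before 24 months has no 24-month value under any method.
- **Low power for recurrence as harm from MANOVA.** Few events would limit a Cox or log-rank test equally.
- **A faulty time origin.** A reader might infer that registration precedes randomisation. The article does not define registration or describe any gap, so this calls only for a definition.

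It can also be said that the fallback covers recurrence, since Kaplan-Meier and log-rank are non-parametric. The clause could be stretched that far, but it is triggered by failed test assumptions, names neither method and sets no censoring rule. Nor is this simply detail left to an analysis plan: the article itself states a method, without exception, that does not fit a listed outcome. Section {20c} does plan exploratory checks of missing-data patterns. These would describe selection but would not bring discarded women back into the model.

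**Conclusion.** The point holds in two parts of different strength.

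The recurrence mismatch is definite and rests on the article's wording alone.

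The complete-vector loss is a real property of the stated method combined with no imputation, but its size is not determinable. It ranges from small, if each outcome is modelled alone at T1 and T2, to a five-visit model keeping about 103-88 of 172 women if a further 5-10% are lost at each later visit. Pooling several outcomes would reduce the number further. These counts are illustrations, not predictions.

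The primary analysis and the sample size are untouched, and recurrence is one of 18 secondary outcomes. This is a correction to the secondary analysis wording, not a threat to the trial's main conclusion.

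**What to change.** 1. **Recurrence.** Except the recurrence-free interval from the MANOVA sentence. Analyse it by Kaplan-Meier with a log-rank test or Cox model, counting time from randomisation and censoring at last contact. State how death without recurrence is handled. Report it as descriptive, because events are likely to be few.
2. **Continuous secondary outcomes.** Analyse each with a likelihood-based linear mixed model containing arm, visit, arm-by-visit, the T1 value and the anthracycline stratum, using all available values. This respects the decision not to impute, because women with some post-baseline visits contribute what was observed. Women with no post-baseline value are not recovered.
3. **Scope.** State which visits enter each outcome's model.

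The cost is revised analysis wording and slightly more programming. The mixed model still relies on an assumption about why values are missing, which the checks planned in section {20c} can inform. No new data are needed. The article says data collection is continuing, so the change can be made before the final analysis.
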